#### Content

The course content was 1) Patient - health care provider relationships, 2) Communication-skills, 3) Patient-worksheets, 4) Current treatment recommendations of type 2 diabetes, and 5) Implementation of the course content in daily practice. The content according to 1), 2), and 3) was based on a course in another trial, Guided Self-Determination, performed in a Danish outpatient diabetes clinic [18]. This intervention showed an effect on perceived autonomy support and improved HbA1c-values among people with type 1 diabetes [18].

#### Patient - health care provider relationships

In a qualitative study design, Zoffmann et al. identified different patient - health care provider relationships with different potential for change among people with diabetes [19]. These relationships: I-you distant provider dominance, I-you blurred sympathy, and I-you sorted mutuality were presented at the first course afternoon. Furthermore, they were included in communication exercises on day 2, 3, and 4. Predominantly meeting the people with I-you distant provider dominance seems to be similar to what Sheldon, et al. define as controlling health care providers [14], and predominantly meeting the people with I-you sorted mutuality seems to be in accordance with autonomy support, if the health care provider is conscious of being neutral and non-judging. The focus of the communication in the I-you sorted mutuality relationships was presented as an empathic approach where the patient's perspectives and values were elicited, acknowledged, and explored.

#### Communication-skills

The communication skills: mirroring, active listening, and values clarification response [18] were presented on the second course afternoon, and were used in different exercises on day 2, 3, and 4.

Mirroring was defined as telling the other person; what you observe, followed by a pause. For an example, repeating the person's last few words in order to make him feel heard, and giving him the opportunity to hear himself. The pause encourages reflection, or perhaps more elaboration [20].

Active listening was defined as telling the other person how you have understood the message in his total communication. The recipient tries to understand the feelings of the sender, and the meaning of the message. Afterwards, without valuing, analysing, or giving advices, the recipient formulates her perception of the message, and sends it back to the sender in order to make him validate the perception [21].

Mirroring is in accordance with simple reflection from motivational interviewing, while active listening is in accordance with summary reflection from the same [14].

The purpose of value clarification is to initiate a process to reconsider and clarify own values, and value clarification response (VCR) is one way to promote this process. The purpose of VCR is to give the patient something to think about concerning the way he acts as well as his attitudes, interests, and assessments. VCR was defined as a reply or a question stimulating reflection and self-insight, and it can often not be answered right away, but has a potential to stimulate a development process [22]. Examples of VCR could be "What does taking preventive medication mean to you?", or "What is important in your life?". Value clarification is also recommended by Sheldon, et al. [14].

#### Patient-worksheets

Three patient-worksheets were introduced with the purpose of stimulating the person with type 2 diabetes's reflection process between the consultations. We stressed that the person should be invited to use worksheets, but that it was entirely their own decision whether they wanted to use them or not. Two of the worksheets were from the method Guided self-determination (GSD) [18], and the action plan was from the Chronic care model (presented in [23]).

One was a reflection sheet with two explorative questions "What do you think has worked, or is working in relation to your life with type 2 diabetes?" and "What do you currently find difficult about living with type 2 diabetes?". The purpose of this work-sheet was to elicit and acknowledge the person's perspective, and to initiate the person's involvement in problem solving. Another worksheet from GSD, "Your plans to change your way of life" was inspired by the Stages of change model developed by Prochaska and Diclemente. It contained a number of statements about behaviours with importance for type 2 diabetes. The person with type 2 diabetes was encouraged 1) to assess what was currently difficult or challenging in his life, and 2) to assess whether he was interested in changing his behaviour or not. This worksheet was intended to give an overview of the person's stages of changes in relation to different recommendations of living with type 2 diabetes, and to acknowledge the option of no willingness to change. Sheldon et al. wrote that people willing to change a behaviour within a 2-4 week period could be thought of as being motivated for making an attempt [14]. The action-plans were introduced in order to develop individual plans, and to support self-initiation for change. The action-plans aimed at clarifying personal goals, and make them concrete, describe how to achieve the goals, identify barriers, and describe how to overcome barriers. When action-plans were introduced at the course "Practice nurses and Type 2 diabetes", it was emphasised that the goals had to be perceived as personally important by the person compiling the action-plan. Hence, it was stressed that the health care provider should ask the question *why *people would like to work with a given action-plan

#### Current treatment recommendations of type 2 diabetes

In order to enhance the nurses' competences to provide clear rationales for advice given, and to provide effective options for change, course day 1 included an update on current treatment recommendations of type 2 diabetes [11]. Furthermore, course day 4 included a workshop aiming to promote discussions among the nurses on how to provide relevant information to the people with type 2 diabetes about the disease and the treatment recommendations. The starting point of the workshop discussion was the patient-worksheet "Your plans to change your way of life".

#### Implementation of the course content in daily practice

Between the course afternoons, we encouraged the participating nurses to fill in worksheets specifically designed for the nurses' own potential changing process. These worksheets were counterpart to the patient-worksheets, but contended issues regarding implementation of the course content in daily practice. On course day 3, we encouraged the nurses to enact a consultation with a person with type 2 diabetes from their own practice.

On course day 3 and 4, half of the time was spent on exchanging experiences from implementing the course content in daily practice, perceived barriers, and feasible actions.

The aim of the ten month-visit in the practice from one of the course-teachers was to discuss the application of the course content in daily practice.

Changed behaviour with regard to autonomy support was self-rated by the nurses 11 months after the core intervention by a mailed questionnaire.

### The outcomes

The outcomes are on patient level. The primary outcomes are: 1) well-being in relation to living with diabetes, which will be measured by Problem Areas in Diabetes scale (PAID), and general well-being measured by the subscale mental health from SF-12v2, and 2) HbA1c(%)- and cholesterol (mmol/l) levels. PAID is a 20-item measure of emotional adjustment to life with diabetes. Construct validity of PAID had been investigated in American, Dutch and Swedish contexts [24-27]. HbA1c and serum-cholesterol are frequently used outcome measures as proxy indicators for prognose in diabetes [28]. HbA1c is a measure of the average plasma glucose concentration over the past two months. Serum-cholesterol is a measure of the level of lipids in the blood, and elevated levels are risk factors of cardiovascular diseases.

Secondary outcomes are 1) perceived autonomy support, 2) type of motivation, and 3) perceived competence regarding living with type 2 diabetes. Based on SDT, Health Care Climate Questionnaire (HCCQ), Perceived Competence for Diabetes Care (PCD) and Treatment Self-Regulation Questionnaire (TSRQ) were developed in order to measure perceived autonomy support, type of motivation, and perceived competence regarding living with type 2 diabetes. TSRQ was validated with regard to construct [29], and in several SDT-studies, structural equation modeling-analyses had offered an appropriate means for confirming construct validity [5-8]. The scales, mentioned, had been translated into Danish following the standardised procedure [18].

### Data

The patient-perceived data will be obtained by a mailed questionnaire, and HbA1c- and cholesterol measurements will be retrieved from the laboratory database in the region. The data from the databases and the questionnaire data will be connected by the unique civil registry number assigned to all Danish citizens. Furthermore, the data will be merged with social data (education, ethnicity, cohabitation) from Statistic Denmark.

### Statistical analyses

The primary analyses will be based on the intention-to-treat principle. As baseline value, the average value of the values measured within the last 12 months before course start will be used. The follow up-value will be the average value of the values measured during the 6 months following 15 months after the core intervention. Effectiveness of the intervention on HbA1c and cholesterol levels will be estimated by the differences between the diabetes populations in the intervention practices and the control practices with regard to 1) mean follow up-HbA1c and cholesterol, and 2) proportions with HbA1c≥8%, and proportions with Total cholesterol ≥5 mmol/l. The differences will be adjusted for baseline values. Differences in the proportions of the diabetes populations with measurements performed will also be assessed. Effectiveness of the intervention on score for PAID, SF-12(mental health), HCCQ, TSRQ and PCSD will be assessed by the difference between the diabetes populations in the intervention practices compared to the control practices 16 months after the core intervention.

Differences in the primary outcomes will be adjusted for age, gender, ethnicity, educational-level, and redeemed diabetes medication in the baseline-period. The analyses will be based on mixed models with including practice as a random factor in order to adjust for correlation within practices. Per-protocol analyses, including practices confirming changed behaviour and people with diabetes confirming participation in a nurse-led diabetes consultation, will be performed. Furthermore, subgroup analyses will be performed with regard to age, gender, and educational-level.

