#### The diabetes population

The diabetes population associated with the included practices in January 2011 was retrieved from the Danish Regional Chronic Database where people with diabetes are identified by an algorithm based on health registers [12]. The health registers consisted of The National Patient Registry, The National Health Insurance Service Registry, the prescription database, and the laboratory databases in the region. People at the ages of 40-74 years in October 2009 who fulfilled one or more of the following criteria: 1) at least one redeemed prescription on diabetes-medication (ACT-code: A10A (insulin) or/and A10B (oral blood-glucose-lowering agents) during October 2008 - October 2009, 2) at least three HbA1c measurements during October 2008 - October 2009, and/or 3) at least one HbA1c ≥6,4% between April 2008-October 2009, were included in the study population (n = 4034).

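### As written, the patient-level covariates apply only to the primary outcomes, so the three motivation scales are compared without them while PAID and SF-12 from the same questionnaire are adjusted

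*Protocol article*

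**What the plan says.** The Outcomes section of the Protocol article places PAID, SF-12 mental health, HbA1c and cholesterol in the primary class. It then lists the rest: "Secondary outcomes are 1) perceived autonomy support, 2) type of motivation, and 3) perceived competence regarding living with type 2 diabetes". These are measured by HCCQ, TSRQ and PCD. The Statistical analyses section writes the last one as PCSD; I take it to be the same scale.

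All five self-reported scales have one source: "The patient-perceived data will be obtained by a mailed questionnaire" (Data). They also share one comparison: "Effectiveness of the intervention on score for PAID, SF-12(mental health), HCCQ, TSRQ and PCSD will be assessed by the difference" between the diabetes populations of the intervention practices, "compared to the control practices 16 months after the core intervention".

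The next paragraph of Statistical analyses sets the covariates: "Differences in the primary outcomes will be adjusted for age, gender, ethnicity, educational-level, and redeemed diabetes medication in the baseline-period". The sentence after it puts the analyses in mixed models with practice as a random factor and does not restrict this to any outcome class.

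Adjustment for baseline, "The differences will be adjusted for baseline values", follows directly on the description of the HbA1c and cholesterol comparisons and comes before any questionnaire score is mentioned. No baseline questionnaire is described for any scale.

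**The concern.** Five scales from one mailing, compared at one time point, fall under two different models, and no reason is given. An analyst who follows the text would adjust PAID for age, gender, ethnicity, education and baseline medication, and would not adjust HCCQ.

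The scales left out carry the theory behind the course: whether training nurses in autonomy support changes what patients perceive and how they are motivated. They rank as secondary, but motivation comes first among the outcomes in the aim and again in the closing statement of what the study will determine.

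Two features make covariates more useful here than in a trial with complete follow-up. Scores exist only for people who return the questionnaire. And the population was attached to practices after the course had ended: "The diabetes population associated with the included practices in January 2011 was retrieved from the Danish Regional Chronic Database", whereas the course ran from October 2009 to September 2010. The balancing described at allocation concerns the distribution of associated patients; no balancing on age, education or ethnicity is mentioned.

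**Working it through.** **No figure to reproduce.** The article gives no precision or power figure for HCCQ, TSRQ or PCD. Its one power figure (90%, at least 30 practices, 0.5% HbA1c) concerns another outcome and comes without SD, intracluster correlation or alpha.

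**Which model applies to which scale, as written**

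| Scale | Class | Source | Practice random factor | Five covariates | Baseline score described |
|---|---|---|---|---|---|
| PAID | primary | questionnaire | yes | yes | no |
| SF-12 mental health | primary | questionnaire | yes | yes | no |
| HCCQ, TSRQ, PCD | secondary | questionnaire | yes | not stated | no |

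The only difference between the rows is the covariate column.

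**Precision.** From the documents: 40 practices and 4034 people, so 4034/40 = 100.85 per practice. Assumed: 20 practices per arm, 70% response (m = 0.7 × 100.85 = 70.6) and intracluster correlation ρ = 0.05.

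- Design effect: 1 + (m − 1)ρ = 1 + 69.6 × 0.05 = 4.48.
- SE of a difference in SD units: √(2 × 4.48 / (20 × 70.6)) = 0.080.
- After adjustment, if covariates explain a share R² of the variance at both levels: SE × √(1 − R²).

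| Assumed R² | √(1 − R²) | SE (SD units) | Reduction |
|---|---|---|---|
| 0 | 1 | 0.080 | – |
| 2% | 0.990 | 0.079 | 1.0% |
| 5% | 0.975 | 0.078 | 2.5% |
| 10% | 0.949 | 0.076 | 5.1% |

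Over ρ from 0.01 to 0.10 and response from 50% to 100%, the unadjusted SE runs from 0.045 to 0.109 SD. The percentage reductions do not change with ρ or response.

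If the covariates explain variance only within practices, the gain is smaller. The squared SE is (2/20) × [ρ + (1 − ρ)/m] = 0.1 × [0.05 + 0.01346]. Cutting the second term by 10% gives 0.1 × [0.05 + 0.01211], and √(0.06211/0.06346) = 0.989, a reduction of about 1.1%.

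**Chance imbalance.** With full response (m = 100.85), the between-arm difference in a standardised covariate has SD √(2 × [1 + 99.85ρ] / (20 × 100.85)).

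- ρ = 0.01: 0.045. The 95% limit is 1.96 × 0.0445 = 0.087.
- ρ = 0.10: 0.104. The 95% limit is 1.96 × 0.1044 = 0.205.

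With an assumed standardised covariate effect of 0.2 on the score, these limits shift the difference by 0.2 × 0.087 = 0.017 to 0.2 × 0.205 = 0.041 SD.

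**Responder mix.** The same product applies: covariate difference between the arms' responders times covariate effect. The documents give neither a response rate nor its likely difference between arms, so this part cannot be sized.

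**The case against.** The best defence is that the article never says the secondary outcomes will be analysed unadjusted. It names covariates for the primary outcomes and is silent on the rest, and an article may leave the secondary models to a fuller plan. That stands to this extent: nothing here is contradictory or wrong, and a decision against adjustment cannot be proved. But the text gives a complete list and ties it to one outcome class, so an analyst working from it would leave HCCQ, TSRQ and PCD without covariates.

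Four stronger readings are tempting, and the documents do not support them.

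- *Clustering is ignored for the motivation scales.* It is not. The practice random factor is stated for the analyses generally.
- *The comparison is biased.* Practices were randomised, so without selective response a comparison without covariates is valid, and its confidence interval already allows for chance imbalance.
- *The motivation scales alone lack a baseline score.* PAID and SF-12 have none described either. The absence is itself an inference, though the January 2011 population link and the single mailing fit it.
- *Baseline HbA1c should enter every questionnaire model.* The diabetes population section admits people on a redeemed prescription alone, and also on one HbA1c from as early as April 2008, before the 12-month baseline window. HbA1c is therefore not available for everyone and would need a missing-value rule.

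It is also fair to say that responder mix affects PAID and SF-12 too. Those scales, however, already receive the covariates.

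**Conclusion.** The point holds as a minor one. Read literally, the plan adjusts two of the five questionnaire scales for patient covariates and leaves three without, for no stated reason. The cost is a standard error about 1-5% larger than it need be, if the covariates explain 2-10% of variance at both levels, and less if they explain only within-practice variance. Chance imbalance at its 95% limit would move a score by about 0.02-0.04 SD. All of these figures rest on assumed values of ρ, R², covariate effect and practices per arm; the precision figures also assume a response rate. The better reason to change the sentence is protection against observed differences among responders, which cannot be quantified here and which adjustment would correct only as far as the five covariates capture them. The validity of the randomised comparison is not in question.

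**What to change.** In the covariate sentence of Statistical analyses, replace *primary outcomes* with *primary and secondary outcomes*. Keep the same five covariates and keep practice as a random factor. If a different model is intended for HCCQ, TSRQ and PCD, state it and give the reason. Do not add baseline HbA1c as a required covariate for the questionnaire scales.

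The cost is a few words. The covariates are already needed for PAID and SF-12, and the Data section links registers and questionnaire through the civil registry number. Any missing register values must be handled for those two scales anyway. Making the change before the questionnaire data are analysed also removes a later choice between adjusted and unadjusted results.

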**Methods/Design:**

The study is a cluster-randomised pragmatic trial including 40 Danish general practices with nurse-led diabetes consultations, and the associated diabetes population. The diabetes population was identified by registers (n = 4034).

The intervention was a 16-hour course with interactive training for practice nurses. The course was delivered over 4 afternoons at Aarhus University and one 1/2 hour visit to the practice by one of the course-teachers over a period of 10 months (0, 2, 5, 10 mths.). The intervention is depicted by a PaT Plot showing the timeline and the characteristics of the intervention components.

Effectiveness of the intervention will be assessed on the diabetes populations with regard to well-being (PAID, SF-12), HbA1c- and cholesterol-levels, perceived autonomy support (HCCQ), type of motivation (TSRQ), and perceived competence for diabetes care (PCD) 15-21 months after the core course; the completion of the second course afternoon. Data will be retrieved from registers and by questionnaires.

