**Figure 1 F1:**
[figure not shown]
**Flow diagram of inclusion, randomisation and allocated intervention received among 258 general practices assessed for eligibility, the former county of Aarhus, DK, 2009**. * People identified by an algorithm based on health registers 2008-2009, and associated with the practices in January 2011.

1) that more than 50% of the people with type 2 diabetes, who had participated in a diabetes-consultation during the past year from the project invitation-date, had attended a consultation with a nurse at least once (confirmed by the practice). A diabetes-consultation was defined as a consultation including examinations, such as blood tests and blood pressure measurement as well as a conversation about living with type 2 diabetes or treatment modalities, according to the three-month consultations in the National guidelines regarding type 2 diabetes care [11],

2) enrolment to the project before registration deadline (three weeks following the date of invitation).

To avoid contamination of the intervention to control-practices, practice registration numbers with the same addresses were defined as one practice. Thus, 40 practices were randomised into two groups, and allocated in a way that the distributions of associated patients were approximately the same in the two groups. Randomisation was performed by a statistician who was blinded to the identity of the practices.

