## Discussion

This paper described an intervention aiming to improve autonomy support for people with type 2 diabetes in general practice, and the methods of evaluating the impact.

Jolly K, el al. [30] and Williams G, C et al. [15] also described the training of professionals in order to achieve autonomy supportive skills. These training programmes also included communication training, updated knowledge about treatment guidelines, focus on interactive learning, and implementation.

In our study, the intervention was offering the training course in a real-world setting. The recruitment strategy was a realistic scenario for future training courses. The design of our study was highly pragmatic [31] as there was no run-in period for the participating nurses, and according to the inclusion of an unselected diabetes population. It was possible to identify an unselected diabetes population owing to the availability of the Danish registers. A limitation is the database's inability to distinguish between types of diabetes, but the number of type 2 diabetes far exceeds the type 1 cases, and the ratio between the types will be equal distributed between the intervention - and the control group. The inclusion of the type 1 population may however, dilute the potential effect of the intervention because type 1 diabetes care is primarily delivered by out-patient clinics. The pragmatic design is challenging with respect to demonstrating the impact of the intervention. Not all the intervention practices participated in all or even in parts of the course. In the study of Williams G, C et al. [15], the health care providers were trained until the intervention could be delivered effectively. The participating practice nurses in our study might not have changed their behaviours, and the study population might not have participated in a diabetes consultation and/or changed behaviour during the time-period. HbA1c- and cholesterol measurements have the ability to change within a short time-period given changed behaviour, but the method and interval to the behaviour change vary. The decision regarding a sufficient follow-up time is therefore challenging. The SDT-based outcomes' ability to measure change is less investigated. Another challenge of demonstrating the impact of the intervention is that an allocation to a control group may have tempted the nurses in the control practices to join another training course.

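### The supplementary per-protocol analysis selects practices on nurses' self-rated change after randomisation, with no stated control counterpart, so its contrast is not protected by randomisation

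*Protocol article*

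**What the plan says.** The Statistical analyses section sets the primary approach: "The primary analyses will be based on the intention-to-treat principle". It then adds a second analysis: "Per-protocol analyses, including practices confirming changed behaviour and people with diabetes confirming participation in a nurse-led diabetes consultation, will be performed". It gives no arm-specific rule and does not say how control practices enter that set.

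The section Implementation of the course content in daily practice explains how the practice criterion is measured: "Changed behaviour with regard to autonomy support was self-rated by the nurses 11 months after the core intervention by a mailed questionnaire". That section is about the nurses who took the course; a few lines earlier it says "we encouraged the participating nurses to fill in worksheets specifically designed for the nurses' own potential changing process".

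The Discussion reports incomplete uptake, "Not all the intervention practices participated in all or even in parts of the course", and says of the other arm that "an allocation to a control group may have tempted the nurses in the control practices to join another training course".

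The Data section names a mailed questionnaire as the source of patient-reported data and the regional laboratory database as the source of HbA1c and cholesterol. Adjustment for baseline values is stated for HbA1c and cholesterol. For PAID and the SF-12 mental health scale, which are also primary outcomes, the article states a between-arm comparison at 16 months and patient-level covariates, but no baseline score.

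**The concern.** A per-protocol set is meant to show what happens where the intervention was delivered. This one selects on something else: whether nurses judged, nearly a year later, that they had changed. That is perceived success, and it can depend on the nurses' motivation, on their patients, and on how their patients were doing. Practices that report change may differ from the rest in HbA1c or well-being for reasons unrelated to the course.

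Control practices had no course to respond to, so the criterion has no natural meaning for them. If it is applied to the intervention arm only, selected practices are compared with all control practices. If it is applied literally to both arms, the only controls kept are those that changed for some other reason, such as another training course, and they do not represent care without training. Neither version preserves the randomised comparison.

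The patient criterion adds a second selection. It too arises after randomisation, and training could alter who attends, or recalls attending, a nurse consultation. It seems obtainable only from people who return the questionnaire, so HbA1c and cholesterol, otherwise available from registers, would be cut to responders.

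**Working it through.** **Figures in the plan.** The article gives no figure for the per-protocol analysis. Its only design figure is 90% power for a 0.5% HbA1c difference with at least 30 practices. SD, ICC and cluster size are not stated, so that figure can be neither reproduced nor refuted, and this point does not depend on it.

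**Inputs from the article.** "Thus, 40 practices were randomised into two groups"; 4034 people, so 4034 / 40 = 100.85, or about 101 per practice.

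**Assumed inputs.** 20 practices per arm (the split is in a figure not shown); HbA1c SD 1.2%; ICC 0.02 to 0.10; share of intervention practices confirming change q = 0.5; correlation rho between confirming change and a better practice HbA1c level; all control practices kept; no true effect.

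**Formula.** Spurious difference = rho × SD × √ICC × φ(z)/q, where z is the threshold that keeps a share q. For q = 0.5, φ(0)/0.5 = 0.399/0.5 = 0.798.

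| ICC | SD × √ICC | rho 0.3 | rho 0.5 |
|---|---|---|---|
| 0.02 | 0.170 | 0.041 | 0.068 |
| 0.05 | 0.268 | 0.064 | 0.107 |
| 0.10 | 0.379 | 0.091 | 0.151 |

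For example, 0.3 × 0.268 × 0.798 = 0.064. Units are HbA1c percentage points. With this sign of rho the error favours the intervention; with the opposite sign it goes the other way.

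**Simulation check.** 3000 trials per setting, ICC 0.05, q = 0.5, unadjusted t-test on practice means:

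| rho | mean spurious difference | type I error, filtered | type I error, ITT |
|---|---|---|---|
| 0 | 0.003 | 5.1% | 5.3% |
| 0.3 | −0.067 | 8.7% | 5.3% |
| 0.5 | −0.110 | 15.0% | 5.3% |
| 0.8 | −0.172 | 32.2% | 4.4% |

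When the same latent filter was applied to both arms (rho 0.5), the difference was 0.003 and the type I error 5.3%. So in this model the distortion comes from the asymmetry between arms. A self-rating of change after a course cannot be made symmetrical, because one arm had no course.

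**Effect of baseline adjustment.** If the practice level is stable and the baseline slope is 0.5 to 0.7 (assumed), a share of 1 − slope, or 0.3 to 0.5, remains. At ICC 0.05 that is 0.064 × 0.3 = 0.019 to 0.107 × 0.5 = 0.054. Over the whole range it is 0.041 × 0.3 = 0.012 to 0.151 × 0.5 = 0.076. No such reduction is stated for PAID or SF-12.

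**The case against.** The strongest reply has four parts.

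- **The article does not say that only the intervention arm is filtered.** This is correct. A reader might infer a written one-arm rule with wholly unselected controls, but the text does not support that. The one-arm reading is drawn from where the self-rating is described, and the patient criterion can apply in both arms. How controls enter may also be set out in a fuller document. The point survives because the practice criterion itself is stated, and neither way of handling controls makes it sound.
- **Only a supplementary analysis is affected.** This is also correct. A reader might infer that the trial's main conclusion is compromised. It is not: intention-to-treat is primary, and the article frames its question as the effect of offering the course. Nothing in the article ties a conclusion to the per-protocol result.
- **The size and sign are assumed.** This stands. SD, ICC, share kept and rho are not in the article, and at rho 0 there is no bias. It would be tempting to say that the bias favours the course, but nurses with harder patients could equally report more change. The main figures are also unadjusted, whereas the plan adjusts HbA1c and cholesterol for baseline.
- **A complier analysis has weaknesses of its own.** This stands in part. If compliance meant attending both core afternoons, partly exposed practices would count as untreated, which strains the exclusion restriction. Defining it as any attendance largely avoids this. The analysis also does not give an effect among patients who attended a nurse consultation.

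**Conclusion.** The concern holds for the supplementary per-protocol analysis. Its practice criterion is a post-randomisation self-rating of success with no stated or natural control counterpart. Its patient criterion is likewise post-randomisation and appears to limit register outcomes to responders. The contrast should not be read as a randomised estimate, and its bias can run either way.

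The size is illustrative. Under the assumptions listed, the unadjusted spurious HbA1c difference is about 0.04 to 0.15 points, or 8% to 30% of the 0.5-point design difference (0.041/0.5 and 0.151/0.5). It is smaller after baseline adjustment and zero if confirming change is unrelated to the practice's outcome level. For PAID and SF-12 no baseline adjustment is stated to reduce it. This is worth correcting before analysis, but it leaves the primary analysis untouched.

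**What to change.** As the supplementary estimate of the effect where the course was taken up, specify a complier-average causal effect:

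- allocation as the instrument, with all practices in both arms retained;
- compliance defined as any course attendance by the practice, with attendance at both core afternoons as a sensitivity analysis;
- the same covariates as in the primary analysis;
- practice-level or cluster-robust inference with a small-sample correction for 40 clusters.

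Report the self-rated-change analysis, if it is kept, as exploratory and non-randomised, and state how control practices enter it.

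The cost is mainly wording. The Discussion and the caption of Figure 1 indicate that participation was known by practice. Session-level attendance, needed for the sensitivity analysis, is not shown and should be confirmed. The confidence interval will be wider, and the estimate relies on allocation having no effect in practices that attended nothing. Dropping the patient criterion frees HbA1c and cholesterol from the restriction to questionnaire responders; the questionnaire outcomes remain limited to responders under any analysis.
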